| **Zielgrößen** | Primäre Zielparameter:   - Reduktion von psychotischen Positiv- und Negativ-Symptomen in SANS und SAPS-Score, - Depressivität (Calgary Depression Scale), - Psychosoziale Funktion (global assessment of functioning, GAF)   Sekundäre Zielparameter:   - Patientenzufriedenheit (Fragebogen für Zufriedenheit mit der stationären Behandlung (ZUF-8) - Lebensqualität (Modular System for Quality of Life) - Selbstwirksamkeitserwartung (Fragebogen zu Kompetenz und Kontrollüberzeugungen) - Mentalisierungsfunktionen (ToM: Reading the Mind in the Eyes Test); Gewahrsein von Emotionen in sozialen Situationen: Levels of Emotional Awareness Scale (LEAS)) |
| **Sicherheit** | Abfrage und Dokumentation unerwünschter Ereignisse zu jeder Visite. Im stationären Verlauf kontinuierliche Beurteilung und Dokumentation der Symptomschwere und etwaiger unerwünschter Ereignisse. Die Teilnehmer werden weiterhin aufgefordert, sich bei Auftreten von unerwünschten Ereignissen zwischen den Visiten umgehend zu melden. |
| **Abbruchkriterien** | Im Einzelfall:   - Suizidalität - Exacerbation der psychotischen Störung - Fremdgefährdung - Neuauftreten von Ausschlusskriterien - Unterbringungsbedürftigkeit nach dem PsychKG.   Insgesamt:  Sollten mehrere Patienten durch die Behandlung destabilisiert werden, und Suizide, Exacerbationen, Gewalt oder Unterbringungen nach dem PsychKG vermehrt auftreten, so kann die Studienleitung über den Abbruch der Studien entscheiden. |
| **Statistische Auswertung** | Die statistische Analyse in Bezug auf die Outcome-  Parameter soll mit Hilfe von T-Tests, ANCOVA und MANCOVA mit Meßwiederholung als Intention-to-treat-Analyse vorgenommen werden, wobei ausscheidende Studienprobanden in die Endanalyse einbezogen werden und die Gründe für das Ausscheiden angegeben werden. |
| **Präklinische Untersuchungen** | Ohne Relevanz |

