The current state of scientific evidence in art therapy in schizophrenia is reported by Ruddy et al. (2005) [4] in a systematic review. Only 2 out of 61 studies were RCTs conducted under sufficient methodological rigour. Green et al. (1987) [5] in their study of 47 outpatients with mixed diagnoses (50% participants with schizophrenia) investigated the effects of 10 sessions of art therapy every 2 weeks compared to patients receiving TAU. Patients receiving art therapy were reported to show improved social interaction and self-esteem and were more likely to complete the trial. Richardson et al. (2002) [6] compared 43 outpatients with chronic schizophrenia after a 12-week course of weekly art therapy with 47 patients treated as usual. Despite high drop-out rates the intervention group experienced a significantly greater reduction of negative symptoms at 6-months follow-up compared to controls. There was a trend for favourable effects of art therapy on social functioning, but not on quality of life and other symptom scales. A number of other studies were non-randomised or case-reports.

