### Definition of Population for Analysis

The intent to treat analysis will be executed with all available patient’s data independent of dropouts and protocol violations. The per protocol analysis will be accepted only for the patients who finished the trial in accordance with the study protocol (valid cases).

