### Analysis of Primary und Secondary Objectives

The primary objective is to determine differential changes of symptom ratings (SANS, SAPS, CDSS) and psychosocial function (GAF score) from baseline. Measurement points are the examinations post-treatment (6 weeks) and at follow-up (12 weeks). Changes are compared between intervention and control groups under consideration of possible confounding variables (repeated measures ANOVA/ ANCOVA, two-tailed level of significance: alpha=0.05).

Secondary objectives and the respective endpoints (satisfaction with care, self-efficacy, social cognition) will be analysed in the same manner. Statistical calculations will be carried out using PASW 18.0.

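### The repeated-measures models named for the intention-to-treat analysis, in their standard form, keep only patients assessed at every visit

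*Protocol*

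**What the plan says.** Section 13.2.2 defines the main analysis set: "The intent to treat analysis will be executed with all available patient’s data independent of dropouts and protocol violations". It sets this apart from a per-protocol analysis of patients who finished in accordance with the protocol.

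The synopsis (row Statistische Auswertung) lists t-tests, ANCOVA and "MANCOVA mit Meßwiederholung als Intention-to-treat-Analyse", and adds "wobei ausscheidende Studienprobanden in die Endanalyse einbezogen werden".

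Section 13.2.3 compares changes from baseline at 6 and 12 weeks, allowing for possible confounders, by "repeated measures ANOVA/ ANCOVA, two-tailed level of significance: alpha=0.05". Secondary endpoints are to be handled in the same way. On software it says: "Statistical calculations will be carried out using PASW 18.0". Section 13.2.6 (Statistical Methods) only refers back to 13.2.3.

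The protocol names no mixed model, imputation rule or other way for an incomplete patient to enter the analysis. It gives no drop-out rate, and section 13.1 performs no sample size estimation.

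**The concern.** The protocol fixes both a population and a model, and in the model's usual form the two do not fit together. Classical repeated-measures ANOVA, ANCOVA or MANCOVA needs one complete row per patient. Someone rated at baseline and week 6 but not at week 12 leaves the analysis altogether, and the week-6 rating goes too. That is not an analysis of all available data. A missing value on any confounder entered as a covariate has the same effect.

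Missing visits are foreseeable. Section 5.1.3 expects some sessions and examinations after discharge, with telephone reminders. Section 8.1 lists loss of contact, serious or repeated adverse events and newly manifested exclusion criteria as reasons for leaving. The synopsis lists suicidality and exacerbation of psychosis as individual stopping criteria, so leaving may be related to the outcome.

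The trial's stated use is to supply effect sizes for a larger efficacy trial (section 13.1). A distorted estimate would carry into that trial's sample size.

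**Working it through.** The plan has no figure of its own to reproduce on this point. Drop-out rates, correlations and effect sizes below are assumptions.

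**1. What the method needs.** SANS/SAPS, CDSS, GAF, MSQoL and FKK are rated at baseline, week 6 and week 12 (Table 1). A standard repeated-measures ANOVA routine, given six subjects at three occasions with one cell removed, refuses to fit because the data are unbalanced. That routine was not PASW, but the need for a complete row belongs to the classical method. Incomplete patients must be dropped first.

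**2. Patients retained.** Take 30 patients (15 per arm, section 3.1) and let each post-baseline visit be missed independently with probability m.

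- Complete at both visits: 30(1 − m)²
- At least one post-baseline visit: 30(1 − m²)

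| m | Complete rows | Any post-baseline visit | Observed but discarded |
|---|---|---|---|
| 10% | 24.3 | 29.7 | 5.4 |
| 20% | 19.2 | 28.8 | 9.6 |
| 30% | 14.7 | 27.3 | 12.6 |

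The last column is the difference between the two before it. It shrinks if losses occur mainly before week 6, because those patients have no post-baseline value under either approach.

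**3. Worst-case bias with no true effect.** Scores have SD 1 and higher is worse. Assumed correlations are 0.5 (baseline with week 6) and 0.6 (week 6 with week 12). Remove from the art therapy arm the worst fraction q at week 6, and leave the control arm complete. With z the (1 − q) normal quantile and φ the normal density:

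- Mean week-6 score of those retained: −φ(z)/(1 − q). For q = 0.20, z = 0.8416 and φ = 0.2800, so −0.2800/0.80 = −0.350.
- Baseline mean of those retained: 0.5 × (−0.350) = −0.175.
- Week-12 mean of those retained: 0.6 × (−0.350) = −0.210.
- Spurious week-6 change: −0.350 + 0.175 = −0.175, about 0.18 SD.
- Spurious week-12 change: −0.210 + 0.175 = −0.035, about 0.04 SD.
- Average of the two visits: (0.175 + 0.035)/2 = 0.105 SD.

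The same formula gives 0.10 SD at week 6 for q = 10% and 0.25 SD for q = 30%.

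These figures are for change from baseline, the quantity that section 13.2.3 names. If the baseline score were a covariate instead, the same complete cases would give a larger week-6 bias, about 0.28 SD at q = 20%.

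**4. Milder drop-out.** Let the chance of missing week 12 in the art therapy arm be 1/(1 + exp(−(a + b × week-6 score))), with b from 0.5 to 1 and a from −1.5 to −1.4. About 19% to 24% of that arm are then lost, and the spurious week-6 benefit is 0.05 to 0.10 SD.

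**5. Drop-out alike in both arms.** With no true effect, the same rule in both arms shifts both means equally, so the bias is zero. With a true week-6 difference of −0.50 SD and the same dependence in both arms, completers give −0.48.

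**6. Comparison.** In these scenarios week-12 missingness depends only on the observed week-6 score. A likelihood-based mixed model is then unbiased, by construction of the scenario.

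**The case against.** - **The method label need not mean listwise deletion.** Section 13.2.3 names no routine, PASW can fit mixed models, and an unseen analysis plan could supply one or an imputation rule. This stands as a limit on certainty: the conflict holds for the standard form. The synopsis's MANCOVA with repeated measures points to that form.
- **Not every named method is affected.** A reader might infer that all the analyses delete any patient with one missing visit. The t-tests and single-visit ANCOVAs in the synopsis lose only patients missing that visit, baseline or a covariate. ZUF-8 is rated only at week 6, and RME and LEAS only at baseline and week 6 (Table 1), so no second post-baseline visit can be lost.
- **Intention-to-treat and per-protocol would not simply merge.** A reader might infer that they would. Section 13.2.2 defines per-protocol by adherence: a patient can attend every rating, violate the protocol, and be in one set but not the other.
- **Power.** For an assumed 0.8 SD effect at two-sided 0.05, power is 56% with 15 per arm, 47% with 12 and 40% with 10. That compares completers with no missing data at all. It does not show what a mixed model would recover, and the protocol makes no power claim.
- **The outside evidence on drop-out is weak.** The remark "Despite high drop-out rates the intervention group experienced" in section 2.1 concerns chronic outpatients with a 6-month follow-up. This trial recruits inpatients, follows them for 12 weeks and uses reminders. It shows that drop-out is a known problem but gives no rate for this trial.

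**Conclusion.** The point holds as a conflict between a stated rule and a stated model. Sections 13.2.2 and the synopsis promise all available data with drop-outs included; the repeated-visit models, in standard form, use assessment completers only.

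The size is conditional. Under independent missingness of 10% to 30% per visit, about 24 to 15 of 30 patients remain, against about 30 to 27 with a mixed model. Bias in week-6 change is about 0.18 SD if the worst 20% of one arm are lost, 0.05 to 0.10 SD under probabilistic one-arm loss, and about zero if loss is alike in both arms. At week 12 the worst case is about 0.04 SD. A reader might take 0.18 SD as the expected bias. The documents do not support that, since they give neither a drop-out rate nor a reason to expect one-sided loss.

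This should be fixed before data are seen. In a pilot without a power claim it does not undermine the trial.

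**What to change.** In section 13.2.3 and the synopsis, replace the repeated-visit model with a linear mixed model for repeated measures (MIXED in PASW 18):

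- outcomes: weeks 6 and 12
- terms: arm, visit, arm-by-visit and baseline score
- covariance: unstructured
- patients: everyone randomised with any post-baseline value, in the assigned arm

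Also:

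- Report the number with no post-baseline value in each arm and add a sensitivity analysis for them. The mixed model alone does not bring them in, so without this the synopsis promise is only partly met.
- State what happens when a further covariate is missing, because a mixed model drops those records too.
- Keep the per-protocol set as section 13.2.2 defines it, and label any completer analysis separately.

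A stated imputation rule would also resolve the conflict.

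The cost is wording only, in software already named. The downside is small: the model assumes that missingness depends only on observed data, and at about 15 per arm it needs a small-sample degrees-of-freedom method.

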### Assessment of Safety

The safety analysis includes all patients with at least one session of art therapy. Safety parameters will be analysed descriptively.

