# Trial Objectives and Purpose

This pilot randomised controlled trial will serve to generate preliminary data on the efficacy and safety of art therapy in patients in acute/ subacute episodes of schizophrenia. Results will allow to prepare a larger multi-centre RCT including the determination of sample-sizes.

**Primary objective** of the pilot study is to determine whether an adjunctive administration of art therapy in addition to TAU will lead to a more substantial symptom reduction in hospitalised patients with schizophrenia compared to standard treatment.

Primary endpoints are the Scale for the assesment of positive symptoms (SAPS) [17], the Scale for the assesment of negative symptoms (SANS) [18] and the Calgary depression rating scale for schizophrenia (CDSS) [19] as well as psychosocial outcome, measured by the Global assessment of functioning scale of the DSM-IV-TR.

**Secondary objectives** refer to the question, which other domains of experience and functioning may be impacted by art therapy. According to previous evidence and theoretical considerations about possible mechanisms of action of art therapy we chose the following constructs and

Secondary endpoints:

- General satisfaction with care (ZUF-8 [22; 23], a modification of the General Satisfaction Questionnaire [22]),
- Quality of life (Modular System for Quality of Life, MSQoL [11]),
- Self-efficacy/ locus of control (Questionnaire for competence and control: Fragebogen zu Kompetenz- und Kotrollüberzeugungen, FKK [20]),
- Mentalising capacity (1.: Reading Mind in the Eyes Test [29, 30]; 2.: Levels of emotional awareness scale, LEAS [34]),

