## Description of control intervention

Patients randomised to the control group receive standard treatment (as usual).

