## Concomitant treatment

All patients receive the indicated standard hospital care adapted to their personal needs.

Study participation does not lead to any alteration of the envisaged treatment. However, the following activities are not allowed for participants of both study arms during the trial period:

- additional art therapy,
- visits to art galleries and museums,
- visits to art education seminars,
- creation of pictorial or sculptural works during occupational or other therapies.

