## Clinical examinations and trial-related deviations of clinical practice

Clinical examinations and symptom ratings, blood tests, pregnancy testing, urine drug screening and ECG belong to necessary routine examinations in schizophrenic patients. Patients with first manifestation of psychotic illness undergo extensive clinical diagnostics including MRI and EEG. Taking a detailed history of the patient and repeated diagnostic interviews also belong to clinical routine. Structured clinical interviews, personality and some of the neuropsychological tests are usually administered according to clinical indication in routine diagnostic procedures. However, the majority of tests and ratings (quality of life, self-efficacy, social cognition) are exclusively performed for scientific purposes. Randomised allocation of treatment is a deviation from clinical practice, the risk of which is minimised by additional visits and standardised ratings of side-effects.

**Table 1:** time schedule for study examinations

| **Instrument** | **Visit 0:**  **Pre-trial** | **Visit 1: Baseline** | **Randomisation**  **and 6 weeks**  **intervention**  **phase** | **Visit 2:**  **Post-treatment**  **(within 7 days after end of intervention)** | **Visit 3: Follow-up**  **(within 7 days after 12 weeks follow-up date)** |
| --- | --- | --- | --- | --- | --- |
| **Informed consent** | x |  |  |  |
| **Inclusion criteria** | x |  |  |  |
| **Demographics** | x |  |  |  |
| **SCID I** | x |  |  |  |
| **SCID II (APD)** | x |  |  |  |
| **SANS/ SAPS** |  | x | x | x |
| **CDSS** |  | x | x | x |
| **GAF** |  | x | x | x |
| **MWT-B** |  | x |  |  |
| **WCST** |  | x |  |  |
| **AVLT** |  | x |  |  |
| **ZUF-8** |  |  | x |  |
| **MSQoL** |  | x | x | x |
| **FKK** |  | x | x | x |
| **RME** |  | x | x |  |
| **LEAS** |  | x | x |  |
| **Medication dose** |  | x | x | x |
| **Documentation of adverse events** |  |  | continuously | x |  |

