# Adverse Events

All adverse events reported during the study must be included in the analysis.

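### The safety analysis is restricted to patients who attended art therapy, so it omits the control arm and contradicts the protocol's own rule that all reported adverse events be analysed

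*Protocol*

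**What the plan says.** Section 13.2.4 (Assessment of Safety) has two sentences. The first fixes the population: "The safety analysis includes all patients with at least one session of art therapy". The second fixes the method: "Safety parameters will be analysed descriptively".

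Section 9 (Adverse Events) opens with a wider rule: "All adverse events reported during the study must be included in the analysis". Section 9.6 requires every adverse event during the study to be entered in the case report form, with no limit by arm.

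Section 3 gives the purpose of the pilot, which is to "generate preliminary data on the efficacy and safety of art therapy" in acute or subacute schizophrenia.

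Section 5.2 gives the control arm standard treatment only. Section 5.3 adds that "the following activities are not allowed for participants of both study arms during the trial period", and additional art therapy is the first item on that list. Section 3.1 plans at least 15 patients per arm.

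On timing, the synopsis (Sicherheit) promises "Abfrage und Dokumentation unerwünschter Ereignisse zu jeder Visite". Table 1 in section 6.6 has a row "Documentation of adverse events" which, as extracted, shows continuous recording, a mark at Visit 2 and nothing at Visit 3.

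**The concern.** A safety population of treated patients is common, but it normally covers patients treated in either arm. Here membership depends on exposure to the experimental therapy alone, so the randomised comparator drops out of the safety analysis. Art-arm patients who attend no session drop out as well.

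This matters because of the kind of harm expected. Section 5.1.1 lists worsening psychosis, suicidal ideation and acts, and aggression. In patients hospitalised for an acute episode, the illness itself can produce all of these. A count from the art arm alone mixes the effect of the therapy with the background course, and the control arm is what would separate them. Section 2.2 partly justifies the trial by the lack of randomised evidence that art therapy is harmless, so omitting the randomised comparison here works against that rationale.

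**Working it through.** The protocol gives no safety event rate for this population, no precision target and no sample-size calculation (section 13.1 says none is made). There is no figure to reproduce.

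**Who can enter the safety set**

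| Group | Planned n | At least one art-therapy session possible under the protocol? | In the 13.2.4 set |
|---|---|---|---|
| Art therapy arm | about 15 | yes | up to 15 |
| Control arm | about 15 | no (sections 5.2 and 5.3) | 0 |

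Share covered: at most 15 / 30 = 50%, with no controls.

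**Section 9 against section 13.2.4.** Section 9 requires all reported adverse events to be analysed. Section 9.6 ensures that control events are reported. Section 13.2.4 admits only attenders. If any control has an event, the two rules cannot both be followed. No other section provides a control-arm table of adverse events.

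**What a one-arm count can show (n = 15)**

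- Chance of at least one event at a 10% rate: 1 − 0.9^15 = 79%. The 10% is the section 7.1 background figure for deterioration under psychotherapy in general, not for art therapy.
- Exact (Clopper-Pearson) 95% limits: 0/15 gives 0% to 21.8%; 3/15 (20%) gives 4.3% to 48.1%.

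**What a control count adds.** The counts below are assumed for illustration. I used the Newcombe interval, built from Wilson limits (l, u) for each arm:

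- lower = d − √[(p1 − l1)² + (u2 − p2)²]
- upper = d + √[(u1 − p1)² + (p2 − l2)²]

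The Wilson limits are 7.1% to 45.2% for 3/15 and 0% to 20.4% for 0/15.

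| Art v control | Difference | 95% CI (points) |
|---|---|---|
| 3/15 v 3/15 | 0 | −28 to +28 |
| 3/15 v 0/15 | +20 | −4 to +45 |

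The set in 13.2.4 reports the same 3/15 in both rows and cannot tell them apart.

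**Precision after the fix.** The half-width is 1.96 × √[2p(1 − p)/15], for an assumed common event rate p:

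- p = 10%: 1.96 × √0.0120 = 21 points
- p = 20%: 1.96 × √0.0213 = 29 points
- p = 30%: 1.96 × √0.0280 = 33 points

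**The case against.** **Control events are collected, and section 9 would bring them into the analysis.** This stands. A reader might infer that adverse events cannot be compared at all. The documents do not support that: the data will exist, and the fault is a contradiction between two sections.

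**Destabilisation is compared elsewhere.** This also stands. Section 13.2.3 compares changes in SAPS, SANS, CDSS and GAF between arms at 6 and 12 weeks, and section 5.5 has these scales rated by assessors blind to allocation. It would be wrong to say that the trial could not detect worsening. Discrete events, such as suicidal acts, aggression and SAEs, have no planned comparison.

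**Each event receives a causality rating (section 9.5), so a one-arm count is not meaningless.** True, but individual judgement is a weak substitute for a concurrent control when the illness produces the same events.

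**Fifteen per arm is too few.** The arithmetic agrees. Even 3/15 v 0/15 would not by itself show harm: the interval includes zero and the two-sided Fisher p is 0.22. That argues for modest claims, not for leaving out controls. A descriptive table by arm needs no more patients.

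**Includes need not mean only.** On that loose reading nothing states whether controls belong to the set, and the sentence still needs correcting.

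**It could be left to the analysis plan.** Section 13.2.4 fixes the population explicitly, so this is a stated rule and not an open detail.

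**Table 1.** A reader might infer that weeks 6 to 12 go without adverse-event questioning. The table is broken in extraction, with a different number of cells in different rows. The synopsis asks at every visit, and section 9.6 covers the whole study. At most this is a cell to check.

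**Conclusion.** The point holds in this form. As written, section 13.2.4 leaves every protocol-compliant control, about 15 of 30 patients, out of the safety analysis. It contradicts section 9 and weakens the safety aim in section 3 for discrete adverse events. It does not affect data collection or the between-arm comparison of symptom scales.

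The exclusion follows from the text and needs no assumption beyond the planned 15 per arm. The illustrative counts and the 20% and 30% rates are assumptions, and the 10% is borrowed from general psychotherapy. Including the controls gives context for the art-arm events. At this size it will not establish harm or its absence.

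**What to change.** - **Section 13.2.4:** define the safety set as all randomised patients, shown by allocated arm. Grouping patients of both arms by treatment received is an acceptable alternative, provided the protocol says where art-arm patients with no session are counted.
- **Tabulation:** report AEs and SAEs descriptively by arm, as patients with at least one event, with the difference and its 95% CI. Say that the comparison is descriptive.
- **Exposure:** keep attendance of at least one session only as a supplementary table within the art arm.
- **Consistency:** check that the revised wording agrees with section 9.
- **Secondary:** look at the adverse-event row of Table 1 in the original document. If Visit 3 is blank there, reconcile it with the synopsis.

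The cost is a sentence or two in 13.2.4 and possibly one table cell. Section 9.6 already requires the data in both arms, so no extra patients or visits are needed.

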## Definition of Adverse Events (AE) concerning the trial

An adverse event is any untoward medical occurrence in a patient or clinical trial subject administered a medicinal product/intervention and which does not necessarily have a causal relationship with this treatment (according to Directive 2001/20/EC).

An AE can therefore be any unfavourable and unintended sign (including abnormal laboratory finding), symptom, or disease temporally associated with the use of a medicinal (investigational) product/intervention, whether or not considered related to the medicinal (investigational) product/intervention.

AEs also include: any worsening (i.e. any clinically significant change in frequency and/or intensity) of a pre-existing condition that is temporally associated with the use of the study drug/intervention; abnormal laboratory findings considered by the reporting investigator to be clinically significant; and any untoward medical occurrence.

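### Section 13.2.4 limits the safety analysis to patients who attended art therapy, so it excludes the control arm and conflicts with section 9

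*Protocol*

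**What the plan says.** Section 13.2.4 (Assessment of Safety) states: "The safety analysis includes all patients with at least one session of art therapy". It adds that the safety parameters are analysed descriptively. No other section defines a second safety set or a display of adverse events by arm.

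The other relevant provisions are:

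- **Control treatment.** Section 5.2 gives controls usual care only. Section 5.3 says that "the following activities are not allowed for participants of both study arms during the trial period", and additional art therapy heads the list.
- **General rule on adverse events.** Section 9 opens with "All adverse events reported during the study must be included in the analysis", without restriction by arm. Section 9.6 requires every adverse event during the study to be entered in the case report forms, again without restriction by arm.
- **Definition.** Section 9.1 describes worsening of a "pre-existing condition that is temporally associated with the use of the study drug/intervention", but its list closes with "and any untoward medical occurrence", which carries no such tie.
- **Aim.** Section 3 names preliminary data on safety, alongside efficacy, as a purpose of the pilot, in preparation for a larger trial.
- **Foreseen harms.** Section 5.1.1 lists exacerbated psychotic symptoms, depression, suicidality and aggression.

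**The concern.** The rule fixes a one-arm safety analysis inside a randomised two-arm trial. That would matter less if the expected harms were peculiar to art therapy, but they are not. Patients are recruited during acute psychotic episodes that need hospital care (section 6.2), and the harms in section 5.1.1 are largely what such an episode can bring unaided. Section 9.5 itself asks the investigator whether the patient's clinical state could have caused the event.

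The error can go either way. Worsening that belongs to the illness may be attributed to art therapy, or a real harm may be dismissed as the course of the illness. Section 7.1 says that reported adverse effects would influence routine treatment, and section 3 wants safety data for planning the larger trial. That planning needs the rate of events under usual care and the difference between arms. A safety analysis that follows section 13.2.4 supplies neither.

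**Working it through.** The protocol states no safety rate and makes no sample size calculation, so there is no figure of its own to reproduce. The check has three steps.

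**Step 1. Who is in the set.** Inputs: at least 15 patients per arm (section 3.1) and about 30 in total (section 3.2), taken as equal arms.

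- Control patients with at least one session under the protocol: 0 of about 15.
- Share of randomised patients left out: 15/30 = 50%. Any patient allocated to art therapy who attends no session is left out as well.

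**Step 2. Whether the sections agree.** Sections 9 and 9.6 together require control events to be recorded and analysed. Section 13.2.4 is the specific rule for the safety analysis and removes them. Both cannot be followed in that analysis.

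**Step 3. What an art therapy count alone can show.** The protocol gives no background rate of worsening, so 5% to 30% is assumed, with no effect of art therapy. The chance of at least 3 worsened patients among 15 is

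P(X ≥ 3) = 1 − Σ (k = 0 to 2) C(15, k) p^k (1 − p)^(15 − k)

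| Assumed background rate p | P(at least 3 of 15) |
| --- | --- |
| 5% | 4% |
| 10% | 18% |
| 20% | 60% |
| 30% | 87% |

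The same count is surprising or ordinary depending on a rate that the safety analysis would not contain.

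Now suppose that 3 of 15 art therapy patients worsen. The exact (Clopper-Pearson) 95% interval runs from the 0.025 quantile of Beta(3, 13) to the 0.975 quantile of Beta(4, 12): 20% (4% to 48%). With a control count the difference can be estimated. Newcombe's interval for d = p1 − p2 uses the Wilson limits (l, u) of each arm:

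- lower limit: d − √[(p1 − l1)² + (u2 − p2)²]
- upper limit: d + √[(u1 − p1)² + (p2 − l2)²]

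The Wilson limits at n = 15 are 0.071 to 0.452 for 3/15, 0 to 0.204 for 0/15, and 0.198 to 0.642 for 6/15.

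| Art therapy | Control (assumed) | Difference, points | 95% interval |
| --- | --- | --- | --- |
| 3/15 | 0/15 | +20 | −4 to +45 |
| 3/15 | 3/15 | 0 | −28 to +28 |
| 3/15 | 6/15 | −20 | −47 to +12 |

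The first row, for example, has lower limit 0.200 − √(0.129² + 0.204²) = −0.042. One art therapy count fits a higher, equal or lower rate than control. All three intervals include zero, so a table by arm is descriptive at this size.

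**The case against.** The strongest reply is that control information is not lost. Section 9.6 puts control events on the case report forms, and section 9 requires them in the analysis. SAPS, SANS and CDSS measure much of the foreseen worsening. They are rated blind in both arms (sections 3.1 and 5.5) and compared at weeks 6 and 12 (section 13.2.3). The synopsis makes exacerbation, suicidality and danger to others individual stopping criteria and promises reasons for dropout. In a pilot of about 30, a table by arm would neither prove nor exclude harm.

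Most of this stands, and it limits the point. Three stronger readings that a reader might infer are not supported:

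- **That no control adverse events will exist, so that the control rate is wholly unknown.** Sections 9 and 9.6 call for them, and the blinded ratings and dropout reasons constrain what could go unseen.
- **That a control patient's relapse can never count as an adverse event.** One clause of section 9.1 links worsening to the intervention, but its closing words do not. The definition of a serious adverse event in section 9.2 covers any untoward occurrence that prolongs a hospital stay.
- **That nothing is collected at follow-up.** The row "Documentation of adverse events" in Table 1 may appear blank at Visit 3, but the table's columns are not reliably aligned in the text available. The synopsis promises "Abfrage und Dokumentation unerwünschter Ereignisse zu jeder Visite", and section 9.6 covers the whole study. This is at most an entry to align.

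The reply does not remove the conflict. Scores at two time points and withdrawal reasons do not count events that arise between visits, resolve and lead to no withdrawal. Section 9 names no analysis set and no comparison, so the specific rule in section 13.2.4 is likely to be the one applied.

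**Conclusion.** The point holds as a conflict between sections and a badly chosen safety set. Followed as written, section 13.2.4 leaves out all controls, about 15 of 30 patients. Adverse event counts then cannot separate worsening from acute schizophrenia from worsening under art therapy. What is chiefly lost is the tabulation by arm of events that do not lead to withdrawal. The data should exist, and the efficacy analysis is unaffected.

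The rule stands in the protocol itself, so an analysis plan that follows it would inherit the problem. The change should be made because it touches a stated aim of the trial, but it does not threaten the trial's validity. The exclusion follows from the text, given equal arms and adherence to section 5.3. The background rates and event counts in the illustration are assumptions.

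**What to change.** 1. Replace the sentence in section 13.2.4 with: *The safety analysis includes all randomised patients; adverse events and serious adverse events are shown descriptively by arm, and patients with at least one session of art therapy are also shown separately.* This agrees with section 9 and keeps the exposed group visible.
2. Add to section 9.1: *In both arms, events count from randomisation to week 12, whatever their relation to the intervention.*
3. Check that the Visit 3 entry for adverse events in Table 1 matches the synopsis.

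The cost is a few lines of text. Section 9.6 already requires the control events on the case report forms, and the synopsis already promises questioning at every visit, so no new data collection is needed.

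There are two downsides. Sessions add up to 12 × 90 minutes = 18 hours of observation in the art therapy arm, so more events may be noticed there. Events first noted in a session should therefore be flagged. Intervals also stay wide at 15 per arm, so the table should be labelled descriptive.
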